### 2.8. Statistical Analyses

All data will be assessed for normality by inspecting visual plots, such as histograms, quantile plots, and Q-Q plots, within each dietary pattern group for each variable. One-way ANOVA or Kruskal–Wallis tests will be used for comparison of CVD risk scores, dietary intake, and cardiometabolic parameters, including all clinical measures, medical/demographics, and blood parameters across dietary pattern groups. Chi-square or Fisher’s Exact tests will be used to compare qualitative dietary intake data and other categorical data across dietary pattern groups. Directed acyclic graphs (DAGs) will be used to display dependencies between outcome (5-year absolute CVD risk and 10-year CVD risk scores), exposure (different categories of dietary patterns determined via classifications presented in Table 1), and confounding/mediating variables to determine the minimum set of variables necessary to control for confounding [33] (Figure 2). Linear regression will be used to account for potential confounding factors described in the DAGs, such as age, sex, alcohol use, smoking status, and physical activity levels. Mediation analysis will be used to estimate the effect of PBDs on CVD risk that is not mediated through BMI [33,34]. Predictably, there will be intrinsic differences between dietary pattern groups, as the study design endeavours to evaluate the true characteristic of each group (chronic diseases, lifestyle choices, etc.). To address this and remove risk of overadjustment, a sensitivity analysis will be performed on potential additional important confounding variables not already identified in the DAGs to assess how robust the results are when comparting the additional confounding factor [35,36]. *p*-values will be adjusted using the Benjamini–Hochberg method to control the False Discovery Rate to 5%.

All statistical analyses will be conducted using StataCorp. 2015. *Stata Statistical Software: Release 14* (College Station, TX, USA: StataCorp LP). Continuous data will be presented as means, SD, median, and interquartile range (25th–75th percentile), and categorical data will be summarised as frequencies and percentages.

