### 2.3. Study Regime

Data will be collected from consented enrolled participants once via two locations on the same day (or no more than 1–2 days apart) after an overnight fast (~10–12 h). First, body composition and bone density will be measured by a trained technician at the Newcastle Bone Density Centre (Waratah, NSW, Australia), and the remaining measurements and data will be collected at the Nutraceuticals Research Program at the University of Newcastle (Callaghan, NSW, Australia). These measurements will be conducted by the lead investigator and include seated blood pressure; waist circumference; diet history; medical, demographic, ethnicity, and physical activity history; and fasted blood samples for lipaemic parameters (total cholesterol, LDL-cholesterol, HDL-cholesterol, triglycerides, and total:HDL-cholesterol ratio), glycaemic parameters (glucose, insulin, and HbA1c), pro-inflammatory mediators (e.g., tumour necrosis factors alpha (TNF-α)), high-sensitivity C-reactive protein (hsCRP), full blood count, vitamin D, and liver function (Figure 1). Table 3 summarises data collected by participants unaided via self-administered questionnaires and data collected with assistance of a study investigator. All questionnaires have been either used in routine clinical care or were previously validated, and references are included within the tables, where appropriate. This cross-sectional study collects information from a singular time-point. Participants will be asked to provide consent to be contacted for potential future research.

The data will be stored on the University of Newcastle’s secure cloud-based system, which is suitable to host files that have large data or computing requirements. All electronic files will be password-protected as will be any study computers or laptops used for data entry in the first instance. The lead study investigator will enter the data, and double data entry and random cross-validation methods on the dataset will be routinely implemented to ensure validity, accuracy, and quality of the data.

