### 2.5. Secondary Outcomes

This study has the following secondary outcomes to investigate across various PBD and regular meat-eating diets: (1) dietary profile, such as dietary intake and food choices, across the five food groups; (2) diet quality and nutritional adequacy; (3) body composition and anthropometric measures; (4) bone mineral density; (5) biochemical parameters; and (6) medical, demographic, lifestyle, and physical activity characteristics. Secondary analyses of duration of following dietary pattern may be explored using a dose–response analysis, with the number of years being the exposure variable. Only sex would be adjusted for, as other variables are influenced by time.

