### 2.6. Clinical Assessments and Laboratory Investigations

#### 2.6.1. Blood Sampling and Analyses

Fasted blood samples will be collected via venepuncture into Vacuette^®^ blood tubes by an experienced phlebotomist. Samples will be centrifuged (Heraeus Biofuge Stratos, Germany, Heidelberg, sourced from Australia) for 15 min at 3000× *g* at 4 °C. Plasma, red blood cells, and buffy coat fractions will be aliquoted and stored at −80 °C until further analysis. Biochemical parameters, such as lipids (total cholesterol, LDL-cholesterol, HDL-cholesterol, triglycerides, and total-cholesterol-to-HDL-cholesterol ratio); glycaemic indices (glucose, insulin, and HbA1c); vitamin D (25-hydroxy vitamin D); full blood count; liver function, and high-sensitive C-reactive protein will be measured on a VP auto analyser using standardized reagents by the commercial pathology service provider NSW Health Pathology–North. Pro-inflammatory mediators, such as interleukin, tumour necrosis factor α, and intercellular adhesion molecule-1, will be quantified by enzyme-linked immunosorbent assay as per the manufacturer’s instructions (Abcam, Cambridge, UK) at the Nutraceuticals Research Program, University of Newcastle, (Callaghan, NSW, Australia). Polygenic risk scores will be measured to predict the likelihood of specific outcomes by including DNA variants in a statistical model.

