The PBDS commenced recruitment on 10 November 2021, and despite having some delay due to the COVID-19 pandemic, we have been able to recruit individuals from the community, with several participants already enrolled into each of the dietary pattern categories. The study remains in the recruitment and data collection phase until at least mid-2023 before data cleaning, coding, and analyses will commence. The study is expected to be completed by mid-2024. As with many observational studies, some of the data collected in this study are self-reported; however, several of the data collection tools employed in this study have been validated in Australian populations. To further mitigate any risk associated with self-reported data, all data are cross-checked by study researchers and clarified (when required) with participants to their ensure accuracy and the correct interpretation of the questionnaires or instructions. As with all cross-sectional population-based studies, caution must be exercised when inferring causation from the results. As detailed in the protocol, appropriate statistical analyses will be conducted to summarise and adjust for the confounding factors and covariates, and a senior biostatistician will be involved in the project.

To conclude, given several strengths and the significance of this study’s findings, albeit with some limitations, analysis of the data arising from this study will likely influence nutrition policy and dietetic practice around the influence of ‘plant-forward’ eating patterns for heart health.

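### 25-hydroxyvitamin D is drawn once per person across about 20 months or more and compared by tests that cannot account for date of draw, so seasonal variation stays in the error term

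*Protocol article*

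**What the plan says.** Section 2.6.1 of the protocol article lists "vitamin D (25-hydroxy vitamin D") among the analytes of the fasted blood sample, and section 2.5 places it under secondary outcome "5) biochemical parameters". Section 2.3 states: "This cross-sectional study collects information from a singular time-point".

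On timing, the Discussion says "The PBDS commenced recruitment on 10 November 2021" and "The study remains in the recruitment and data collection phase until at least mid-2023". It also reports recruitment in parallel, "with several participants already enrolled into each of the dietary pattern categories".

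On analysis, section 2.8 says "One-way ANOVA or Kruskal–Wallis tests will be used for comparison of CVD risk scores, dietary intake, and cardiometabolic parameters", and extends this to a list "including all clinical measures, medical/demographics, and blood parameters across dietary pattern groups". The directed acyclic graphs in the same section have only the two CVD risk scores as outcomes. The adjustment variables named there and under Figure 2 are age, sex, alcohol, smoking and physical activity. Season, month and visit date are not mentioned anywhere, and no balancing of visit dates across diet groups is described.

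**The concern.** Vitamin D status depends partly on sun exposure and can be expected to move through the year. A person sampled once contributes the level of whatever month they attended. Over a window of more than one year, the spread of values within each diet group therefore mixes differences between people with differences between months. A one-way test has no place for the date, so the month-to-month part is counted as unexplained error. This costs precision even when every group is sampled on the same calendar.

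A second consequence is conditional. Participants are community volunteers reached through media, flyers and social groups, and the target is 48 in each of five groups. If one group happens to be sampled more in warm months than another, the season difference enters the group contrast, and the one-way test cannot separate it from diet. The Benjamini–Hochberg adjustment in section 2.8 deals with the number of tests. It does not remove confounding by date.

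**Working it through.** **Inputs from the article.** 48 per group in five groups; Δ = 3.33 and SD = 5.77 for the CVD risk score; alpha 0.05; power 80% (all section 2.7). Recruitment starts on 10 November 2021 and runs to at least mid-2023 (Discussion).

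**Assumptions.** The article gives no seasonal amplitude or SD for vitamin D. Season is taken as a sinusoid of amplitude A, in units of the within-season SD, with A from 0.25 to 0.75. For the simulation the peak is put at mid-February and the window is closed on 30 June 2023.

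**1. The plan's own figure.** n per group = 2 × (1.96 + 0.8416)² × (5.77 / 3.33)² = 2 × 7.849 × 3.002 = 47.1, rounded up to 48. Power at 48 per group is 0.807. The stated 240 reproduces. The standardised difference is 3.33 / 5.77 = 0.577 SD. It is borrowed below only as a yardstick, because the article claims no power for vitamin D.

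**2. Length of the window.** 10 November 2021 to 1 June 2023 is 18.7 months; to 30 June 2023 it is 19.6 months. With the article's proviso that this is a minimum, it is about 20 months or more, so each group can be sampled in several seasons.

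**3. Precision loss with dates spread evenly over the year.** A sinusoid of amplitude A adds variance A²/2. Season share = (A²/2) / (1 + A²/2). The effective difference becomes 0.577 / √(1 + A²/2). For A = 0.5: 0.125 / 1.125 = 11%, and 0.577 / 1.061 = 0.544.

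| A | Season share of variance | Power, season removed | Power, season left in |
|---|---|---|---|
| 0.25 | 3% | 0.81 | 0.80 |
| 0.50 | 11% | 0.81 | 0.76 |
| 0.75 | 22% | 0.81 | 0.70 |

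**4. False positives when diet has no effect.** 4,000 simulated studies per cell, five groups of 48, nominal 5%. In the unequal scenarios one group has the stated share of visits in the warm half-year and the other four have 50%.

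| Visit dates | A = 0.25 | A = 0.50 | A = 0.75 |
|---|---|---|---|
| Same distribution in all groups | 4.5% | 5.1% | 4.7% |
| 65% against 50% | 4.9% | 5.8% | 7.7% |
| 80% against 50% | 6.6% | 10.3% | 18.4% |

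The spurious mean difference at 80% against 50% is 0.09, 0.18 and 0.27 SD. With sine and cosine terms of the visit date in the model, the rejection rate stays between 4.3% and 5.3% in every cell.

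**The case against.** The strongest reply is that this is a covariate choice for one secondary biomarker, of the kind a condensed article leaves to an analysis plan. Section 2.8 also foresees a sensitivity analysis on further, unnamed confounders, and the Discussion promises adjustment with a senior biostatistician. Part of this stands: nothing in the article forbids a date term, and a separate plan may add one. But section 2.8 does name the test for blood parameters, and that test takes no covariate. The regression is tied to graphs whose outcomes are the CVD risk scores. Even if it were extended to blood parameters, season is not among its listed variables.

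It is also fair to say that a one-way test which omits a predictor remains valid when dates are balanced. That is conceded: only precision is lost.

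Three stronger readings are tempting, and the article does not support them.

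- A reader might infer that vitamin D carries the nutritional-adequacy objective, or that a planned adequacy cut-off is distorted. Section 2.5 lists adequacy separately from the biochemical parameters, section 2.6.4 assesses it from intake against reference values, and no serum cut-off is planned.
- A reader might infer bias from the surplus of warm months in the window (about 61% of days to end June 2023, with the assumed mid-February peak). A surplus common to all groups does not by itself bias a contrast between them.
- A reader might infer that a false diet difference is to be expected. It needs groups to differ in sampling months. The article reports parallel recruitment and gives no month-by-group figures, so this is a possibility only.

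**Conclusion.** The point holds as a minor one. For 25-hydroxyvitamin D, the tests named in section 2.8 leave seasonal variation in the error. At an assumed amplitude of 0.25 to 0.75 within-season SD, this is about 3% to 22% of the total variance and lowers power for a 0.577 SD difference from 0.81 to between 0.80 and 0.70. The direction follows from single sampling over several seasons if the marker is seasonal. The size rests on an amplitude that the article does not give.

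Confounding of diet by season is conditional on unequal sampling months. Marked inflation of the 5% level appears only with strong imbalance (80% against 50%) and an amplitude of at least 0.5 SD. With equal date distributions the level is kept.

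Vitamin D is not among the variables section 2.4 lists for the Framingham score, and section 2.7 sizes the study on that score. The primary outcome and the sample size are therefore unaffected.

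**What to change.** In section 2.8, take 25-hydroxyvitamin D out of the one-way comparison. State that it will be compared by linear regression on diet group with sine and cosine terms of the blood-draw date, or with season as a factor. Report season-adjusted group means with confidence intervals, and tabulate month of draw by diet group so that a reader can see whether timing differed.

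The cost is two extra model terms taken from the visit date, with no new data collection. The article places analysis after recruitment closes, so the change can be specified before the data are examined.

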## Abstract

Plant-based diets (PBDs) emphasise higher intakes of plant foods and lower intakes of animal foods, and they have been associated with reduced cardiovascular morbidity/mortality and lower cardiovascular disease (CVD) risk factors. Evidence is limited regarding the dietary profile, diet quality, and nutritional adequacy of PBDs, including their impact on CVD risk compared with traditional meat-eating diets in Australians. The PBD Study (PBDS) is a cross-sectional study that will recruit 240 adults from the Hunter region (NSW) without known CVD who are habitually consuming vegan (no animal flesh/animal products), lacto-ovo vegetarian (dairy and/or eggs only), pesco-vegetarian (fish/seafood only), or semi-vegetarian (minimal animal flesh) diets or are a regular meat-eater. To investigate dietary profile, diet quality, nutritional adequacy, and CVD risk, questionnaires (medical history, demographics, and physical activity), blood samples (biomarkers), physical measures (anthropometry, blood pressure, body composition, and bone density), and dietary intake (food frequency questionnaire and diet history) will be collected. One-way ANOVA and Kruskal–Wallis tests will compare the CVD risk and other quantitative measures, and Chi-square or Fisher’s Exact tests will be used for qualitative data. Directed acyclic graphs will determine the confounding variables, and linear regression and mediation analyses will account for the confounders and estimate the effect of dietary patterns on CVD risk. *p*-values will be adjusted using the Benjamini–Hochberg method to control the False Discovery Rate to 5%.

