#### 2.6.3. Body Composition

Body mass and composition will be measured via dual-energy X-ray absorptiometry (DXA) using the GE Lunar Prodigy DXA machine (narrow angle fan beam technology) at the Newcastle Bone Density Centre, which is a private medical imaging centre in Newcastle. Body mass (kg), fat mass (kg), fat percentage, fat mass index, lean muscle mass (kg), lean muscle mass percentage, lean muscle mass index, body mass index (kg/m^2^), android/gynoid fat tissue distribution (% and ratio), waist-to-hip ratio, relative skeletal muscle index (kg/m^2^), bone mass (kg), and bone mineral density (g/cm^2^) will be quantified. At the Newcastle Bone Density Centre, all scans will be performed by qualified and experienced clinicians. Participants will attend the centre once, either on the same day or no more than 1–2 days of their clinic appointment at the University of Newcastle.

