**Figure 2 nutrients-15-02850-f002:**
[figure not shown]
Directed acyclic graph showing independence among potential confounding and mediating variables on the association between PBDs and CVD risk. Confounding factors are age, sex, alcohol use, smoking status, and physical activity levels, and BMI is a mediator. BMI, body mass index; PBDs, plant-based diets; CVD, cardiovascular disease.

**Table 2 nutrients-15-02850-t002:** Classification of dietary pattern groups by the number of time(s) foods are consumed, on average, per week.

	Vegan	Lacto-Ovo Vegetarian	Semi-Vegetarian	Pesco-Vegetarian	Regular Meat-Eater
Times per week consumed:					
Red meats:	0	0	≤1	0	0 or ≥1
Beef, kangaroo, veal, lamb, pork, etc.					
White meats:	0	0	≤1	0	0 or ≥1
Chicken, turkey, duck, etc.					
Processed/cured meats:	0	0	≤1	0	0 or ≥1
Bacon, corned beef, luncheon meats, such as ham, prosciutto, salami, etc., sausages, frankfurters					
*Seafood:* Fish (including tinned), crustaceans, oysters, squid, mussels, etc.	0	0	0 or ≤1	≥1	0 or ≥1
**Total of above categories**	0	0	≤2	≥1	≥7
Usual eating habits					
Animal-based dairy products (milk, cheese, ice-cream, butter, cream, margarine blends, etc.)	Nil	Y	N/A	N/A	N/A
Eggs	Nil	Y	N/A	N/A	N/A

Defining characteristics of dietary patterns are adapted from those previously implemented in Australian cohorts by Ferguson et al. [12] and Mihrshahi et al. [10]. ‘N/A’ denotes characteristics that were not relevant and, thus, not used for categorizing into respective diet groups.

**Table 3 nutrients-15-02850-t003:** Questionnaires, histories, measures, and biochemical samples completed by participants unaided and with assistance of a study investigator.

Item	Measures and Tools	Collected by Researcher or Participant ^1^
Medical history, medication/supplement use, and family medical history	Medical and Demographic Questionnaire	Participant
Demographics, ethnicity, socio-economic status, education history, employment history, smoking history, habitual alcohol intake, marital status, household food, and social history	Medical and Demographic Questionnaire	Participant
Physical activity	International Physical Activity Questionnaire (IPAQ-Long Form 2002) [13]	Participant
Dietary intake (qualitative), diet quality	Australian Eating Survey Food Frequency Questionnaire (AES FFQ) [14]	Participant
Food and nutrient intake (quantitative) and dietary pattern characteristics	Diet history via Accredited Practicing Dietitian	Researcher

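### Section 2.8 explicitly assigns only an unadjusted group test to the body composition, bone density and blood outcomes, so an uneven age or sex mix can pass for a diet effect

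*Protocol article*

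**What the plan says.** Section 2.5 lists the secondary outcomes to be examined across the diets. Among them are "3) body composition and anthropometric measures; (4) bone mineral density; (5) biochemical parameters". Section 2.6.3 lists the body composition measures, which include "fat mass (kg), fat percentage, fat mass index, lean muscle mass (kg), lean muscle mass percentage, lean muscle mass index"; bone appears as bone mass in kg and density in g/cm².

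Section 2.8 assigns one-way ANOVA or Kruskal–Wallis to the CVD risk scores, dietary intake and cardiometabolic parameters, "including all clinical measures, medical/demographics, and blood parameters across dietary pattern groups". It then describes directed acyclic graphs whose outcome is given in brackets: "outcome (5-year absolute CVD risk and 10-year CVD risk scores". The adjusted model follows: "Linear regression will be used to account for potential confounding factors described in the DAGs, such as age, sex, alcohol use, smoking status", together with physical activity. That sentence names no outcome. The caption of Figure 2 describes the association between plant-based diets and CVD risk and states: "Confounding factors are age, sex, alcohol use, smoking status, and physical activity levels, and BMI is a mediator". The Abstract says that "linear regression and mediation analyses will account for the confounders and estimate the effect of dietary patterns on CVD risk".

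Section 2.9 promises adjustment for health and demographic characteristics and refers the reader back to the statistical section. The Discussion promises adjustment for confounders and covariates as set out in the protocol. Neither names an outcome. The only covariate named for a secondary analysis is sex, in the optional analysis of time on the diet (Section 2.5).

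**The concern.** Many of the secondary clinical outcomes can vary with sex and age. The sample includes both sexes and, under Table 1, ages 35 to 75. Participants join the groups by the diet they already eat and are recruited through flyers, media and word of mouth (Section 2.2). No matching, quota or stratification by age or sex is described. The protocol names age and sex as confounders and expects the diet groups to differ intrinsically (Section 2.8).

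If one diet group has more women or is younger than another, an unadjusted comparison of lean mass, bone density or a blood marker mixes that difference with any effect of diet. It can create a difference or hide one. The findings are meant to inform dietary guidelines (Section 2.10.4), so a wrong reading on muscle, bone or blood measures would carry weight. The Benjamini–Hochberg step does not help here: it deals with the number of tests and leaves confounding untouched.

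**Working it through.** **Which analysis goes with which outcome**

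| Outcome | Unadjusted group test | Adjusted model explicitly tied to it |
|---|---|---|
| 5- and 10-year CVD risk | Yes (2.8) | Yes (2.8, Figure 2, Abstract) |
| Body composition, bone density, biochemistry | Yes (2.8) | None named |

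The CVD graph cannot simply be reused for the second row. It treats BMI as a mediator, but BMI is itself one of the body composition measures in Section 2.6.3.

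**The plan's own figure.** Section 2.7 gives 48 per group for a difference of 3.33 with SD 5.77, 80% power and level 0.05 (two-sided assumed). n = 2 × (1.96 + 0.84)² × 5.77² / 3.33² ≈ 47.1, rounded up to 48, so it reproduces. It concerns the primary outcome and is used below only as the group size.

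**Illustration 1: two groups, lean mass, no diet effect.** The documents give neither the sex mix nor the sex gap, so all inputs except n = 48 are assumptions: male–female gap 16 kg, within-sex SD 7 kg.

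With p the share of men, the group variance is 7² + 16² × p(1 − p), the spurious difference is 16 × (p₂ − p₁), and SE = √[(V₁ + V₂)/48].

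- 80% against 55% women (p = 0.20 and 0.45): V₁ = 49 + 256 × 0.16 = 89.96; V₂ = 49 + 256 × 0.2475 = 112.36. Difference 16 × 0.25 = 4.0 kg; SE = √(202.32/48) = 2.05. Two-sided rejection at 0.05 (normal approximation): 0.495.
- 65% against 55% women (p = 0.35 and 0.45): V₁ = 49 + 256 × 0.2275 = 107.24; V₂ = 112.36. Difference 1.6 kg; SE = √(219.60/48) = 2.14. Rejection: 0.116.

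**Illustration 2: the planned five-group ANOVA.** Let g be the sex gap in within-sex SDs and sᵢ the share of women in group i. Group means are −g·sᵢ, the average variance is v = mean[1 + g²sᵢ(1 − sᵢ)], and the noncentrality is λ = 48 × Σ(mᵢ − m̄)²/v with 4 and 235 degrees of freedom.

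Assumed shares of women: 80/70/70/70/50% (first group vegan, last meat-eaters). For g = 1, Σ(mᵢ − m̄)² = 0.048, v = 1.208 and λ = 48 × 0.048/1.208 = 1.91.

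| Sex gap g (SD) | Spurious vegan–meat-eater difference (SD) | Rejection, unadjusted |
|---|---|---|
| 0.5 | 0.15 | 8% |
| 1 | 0.30 | 16% |
| 1.5 | 0.45 | 28% |
| 2 | 0.60 | 39% |

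With a milder mix (75/65/65/65/55%) the range is 6% to 17%. With 80% women in every plant-based group and 50% among meat-eaters it is 9% to 60%. In 4,000 simulated studies per setting with the 80/70/70/70/50% mix, adding sex as a covariate brought rejection to 5.2% (g = 1) and 4.6% (g = 2). With equal mix (70% women in every group, g = 2) the unadjusted test rejected in 4.9%.

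**The case against.** The strongest reply is that the protocol nowhere rules out adjustment. The regression sentence in Section 2.8 names no outcome, Section 2.9 and the Discussion promise adjustment in general terms, and a condensed article may leave the covariates of each secondary outcome to an analysis plan. A reader might infer that these outcomes will be reported unadjusted and nothing more; the documents do not say that. What remains is that a test is named for these outcomes, that the confounder set and the Abstract's regression are tied to CVD risk, and that Section 2.9 points to Section 2.8 as the place where adjustment is reported.

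A reader might also infer that the trouble comes from using absolute units. That does not hold: Section 2.6.3 also lists percentages, indices and ratios, and kg or g/cm² do not describe blood markers. Percentages and indices can still differ by sex and age, so the need for adjustment does not rest on units.

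The secondary aims are partly descriptive, and an unadjusted table is legitimate for description. The Discussion also warns against inferring causation. Both points stand, but neither tells the reader how much of a group difference is age or sex.

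Finally, the illustrations rest on assumed values. They cover sex only, not age, and leave out the Benjamini–Hochberg step, which would generally make rejection of a single test less frequent without shrinking the spurious difference. The first uses a strongly sex-dependent measure and a two-group test.

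**Conclusion.** The point holds as a defect in what Section 2.8 fixes: for body composition, bone density and biochemistry, the only explicitly assigned analysis is an unadjusted group test, in self-selected groups for which the protocol itself names age and sex as confounders.

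The consequence is conditional. Bias arises only if the age or sex mix differs between diet groups, and the documents give no mix by group. It would therefore go too far to say that these results will be biased, or in which direction. Under the assumed sex imbalances, false rejection in the five-group ANOVA runs from about 6% to 60% against a nominal 5%. In the two-group lean mass example it is about 12% to 50%. These figures show that the effect can be material; they are not forecasts for this study.

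**What to change.** State in Section 2.8 that each continuous secondary clinical outcome is compared between diet groups by linear regression adjusted for at least age and sex. Justify the adjustment set for that outcome instead of carrying the CVD-risk set over unexamined; for example, body composition outcomes should not be adjusted for BMI. State that the adjusted contrast is the reported result for any diet comparison, and keep the ANOVA or Kruskal–Wallis table as description.

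The cost is small: extra regressions and a short rationale for each adjustment set. Age and sex are already needed for the Framingham equation (Section 2.4), so no new data are required.
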